**Methods/Design:**

We will conduct a multicentre, randomized, unblinded, controlled trial with three parallel arms (1:1:1). 1,145 women will be randomized at three hospitals in South Africa. Women will be eligible for inclusion if they are ≥18 years old, nulliparous, gestational age ≥ 35 weeks, have a singleton pregnancy in cephalic presentation and vaginal delivery anticipated. Women with chronic medical conditions or obstetric complications are not eligible. If eligible women are undelivered following 15-30 min in the second stage of labour, they will be randomly assigned to: 1) GAP in the upright posture, 2) upright posture only and 3) routine practice (recumbent/supine posture). The primary outcome is the mean time from randomization to complete delivery. Secondary outcomes include operative delivery, adverse neonatal outcomes, maternal adverse events and discomfort.

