### Study participants

All women attending participating hospitals for delivery (who meet the inclusion criteria) during the study period will be approached for participation in this study.

The eligibility criteria are:Equal to or greater than 18 years old;Nulliparous women;Gestational age ≥ 35 weeks;Singleton pregnancy;Vaginal delivery anticipated;Cephalic fetal presentation;Baby’s heartbeat detected;No chronic medical conditions, including heart disease, epilepsy, hypertension, diabetes mellitus and renal disease;No obstetric complications, including hypertensive disorders of pregnancy, cephalo-pelvic disproportion, antepartum haemorrhage, intra-uterine growth restriction, fetal distress, intra-amniotic infection; andWilling and able to provide consent

Women whose labours are induced or augmented, or women with HIV, are not excluded from this trial. However, this information will be captured in the trial forms.

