### Recruitment and screening procedures

In participating facilities, nulliparous women ≥18 years old will be approached with information about the trial. Women who are in latent phase of labour and who meet the eligibility criteria will be fully counselled and informed about the trial. The following guidelines will be used for screening:The woman should be sufficiently comfortable to make an informed choice.Information should be provided in her home language.She will be given an information sheet and offered time to reflect and ask questions, or to consult with family members.If she agrees, she will sign the informed consent formIlliterate participants will have the consent form read to them.Verbal consent will be witnessed by an independent signatory.Following receipt of the signed consent form, baseline demographic and clinical data will be recorded on the screening form.Screened women will be given a screening number, including women who decline to take part and those who are not eligible. All screening forms will be kept by the study team.

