### Study outcomes

The primary outcome is defined as mean time (minutes) from randomization to delivery.

Secondary outcomes include the following:Delivery outcomes:oNo spontaneous delivery within 15 min of randomization;oOperative delivery (vacuum, forceps or caesarean section); andoEpisiotomy or 2nd/3rd degree tears.Neonatal outcomes: oCord blood pH < 7.2;o5-min Apgar score <7;oNeonatal injury;oNeonatal encephalopathy;oAdmission to neonatal high care nursery for ≥24 h; andoNeonatal death.

Mothers will also be asked to grade their discomfort experienced during the second stage of labour. All adverse events and serious adverse events will also be recorded.

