### Statistical methods

The sample size has been calculated to be powered to detect a reduction in the primary outcome of mean time (minutes) from randomization to delivery of > =3 min. A reduction of > =3 min was used due to the findings of the study by Api et al (2009) [31], that reported a time from randomization to delivery of 23.1 min (SD 12.2 min) in the control group (*N* = 56), and 18.6 min (SD 9.5 min) in the fundal pressure group (*N* = 34). We assumed that upright posture alone would likely lie between these two (i.e. approximately 20.0 min). Using the Bonferroni rule to control for multiplicity, alpha is divided by the number of comparisons (0.05/3 ≈ 0.02). We assumed a power of 90 % and alpha of 95 %. The study therefore requires 347 women in each arm, i.e. 1,041 women for all three arms. To allow for 10 % non-compliance, we aim to recruit 382 in each arm. The final sample size for the whole study is 1,145 women.

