### Data analysis

Data will be generated from the on-line data management system and analysed in SPSS. The primary analysis will be based on all subjects with outcome data available. Any participants with protocol violations, including women who no longer wish to receive their allocated intervention but are prepared to have data collected, will be analysed in the group to which they were allocated (intention-to-treat). Data from subjects who withdraw their consent will be excluded from the analysis and considered as lost to follow-up.

Baseline characteristics will be compared between groups to confirm the effectiveness of the randomization process in creating similar groups. Numbers and baseline characteristics of women lost to follow-up will also be compared between study groups to detect any imbalances.

Most study outcomes are categorical variables. For these types of variables, the number of subjects, number of missing values and percentages will be reported. Categorical variables will be compared between study arms as risk ratios with 95 % confidence intervals.

For continuous variables, e.g. time to delivery, the number of subjects, and number of missing values, minimum, maximum, means and standard deviations will be reported. Appropriate transformation of non-normal or skewed measurement will be performed. Means will be compared using t-tests for two independent samples, and 95 % confidence intervals will be calculated. If transformations do not generate a distribution approaching normality, medians and interquartile range (IQR) will be reported. The primary outcome of the study is “mean time (minutes) from randomization to delivery”. The survival technique log-rank test will also be used to compare the survival rates of the three groups, pairwise. Results will be reported according to CONSORT guidelines [22].

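### The comparison of mean time to delivery is fixed as an unadjusted t-test although prognostic baseline data are collected, which gives up a modest and so far unquantified amount of precision

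*Protocol article*

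**What the plan says.** - **Outcome** (Study outcomes): "The primary outcome is defined as mean time (minutes) from randomization to delivery".
- **Method** (Data analysis): "Means will be compared using t-tests for two independent samples, and 95 % confidence intervals will be calculated". A second test is added: "The survival technique log-rank test will also be used to compare the survival rates of the three groups, pairwise". Neither comes with a covariate. Skewed measurements are to be transformed, with medians and interquartile ranges reported if that fails.
- **Stated use of baseline data** (Data analysis): baseline characteristics are compared between arms as a check on the randomization, and between arms among women lost to follow-up. No other use is given.
- **Data collected.** Women with induced or augmented labour, or with HIV, are admitted, and Study participants adds: "However, this information will be captured in the trial forms". After consent, "baseline demographic and clinical data will be recorded on the screening form" (Recruitment and screening procedures), which is before randomization.
- **Entry rule** (Abstract, Methods/Design): "If eligible women are undelivered following 15-30 min in the second stage of labour, they will be randomly assigned".
- **Allocation** (Sampling and allocation): the envelopes are prepared separately for each study site.

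**The concern.** How long a woman still has to go to delivery plausibly depends on features known at randomization, such as whether labour was induced or already augmented, and how long she has been in second stage. An unadjusted t-test leaves the variance due to these features in the standard error. A linear model with the same covariates targets the same difference in mean minutes and usually estimates it more precisely, with no extra women. All three pairwise comparisons are affected. At stake is a somewhat wider interval and somewhat lower power than the same data could give.

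**Working it through.** **Inputs (Statistical methods section).** The target is to "detect a reduction in the primary outcome of mean time (minutes) from randomization to delivery of > =3 min". The cited study "reported a time from randomization to delivery of 23.1 min (SD 12.2 min) in the control group" and 18.6 min (SD 9.5) with fundal pressure. Upright posture alone is put at about 20.0 min. Alpha is 0.05/3, rounded there to 0.02, and power is 90%. The stated size is 347 per arm, raised to 382 for 10% non-compliance. Sidedness is not stated; two-sided is used here because it reproduces the plan's figure.

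**Step 1: the plan's own figure.** n = (12.2² + 9.5²)(z₀.₉₉ + z₀.₉₀)² / 3² = 239.09 × (2.326 + 1.282)² / 9 = 345.8, so 346 per arm against the stated 347. Power at 347 is 90.1%. Then 347 × 1.1 = 382. The stated size therefore belongs to an unadjusted comparison and delivers its power without covariates.

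**Step 2: effect of adjustment.** If covariates explain a share R² of the variance, SE = √[239.09 × (1 − R²) / n]. Power is Φ(δ/SE − 2.394), where 2.394 is the two-sided critical value at 0.05/3. The equivalent number per arm is 382/(1 − R²). R² is **assumed**. With n = 382:

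| R² | SE (min) | Equivalent n per arm | Power, 3 min | Power, 2.7 min | Power, 1.4 min |
|---|---|---|---|---|---|
| 0 | 0.791 | 382 | 91.9% | 84.6% | 26.6% |
| 2% | 0.783 | 390 | 92.5% | 85.4% | 27.2% |
| 5% | 0.771 | 402 | 93.3% | 86.6% | 28.2% |
| 10% | 0.751 | 424 | 94.6% | 88.6% | 29.9% |
| 15% | 0.729 | 449 | 95.7% | 90.5% | 31.8% |

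The 2.7-min column is 3 × 0.9: the target diluted by the plan's 10% non-compliance under intention-to-treat, if non-compliant women gain nothing. The 1.4-min column is 20.0 − 18.6, GAP versus upright alone. The plan gives no SD for upright posture, so the same two SDs are used.

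**Step 3: what R² is plausible?** The base variance is 239.09/2 = 119.5.
- *Elapsed second-stage time.* If uniform over 15 to 30 min (assumed), its SD is 15/√12 = 4.33. A slope of 0.25, 0.5 or 1 min per elapsed minute gives R² = (slope × 4.33)²/119.5 = 1%, 4% or 16%.
- *Induction or augmentation.* With prevalence p of 30% to 50% (assumed) and a difference d between the two groups of women, R² = p(1 − p)d²/119.5. A 3-min difference gives 1.6% to 1.9%; a 5-min difference gives 4.4% to 5.2%.

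So 2% to 5% is easy to reach, while 10% to 15% needs strong predictors.

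**Step 4: what is known to be recorded.** Induction and augmentation status is captured, but without a stated time relative to randomization, and Arm 3: Routine practice allows oxytocin at any stage of labour. No section says that second-stage onset or elapsed minutes are recorded. The items that Follow-up procedures requires on the quality-control recordings are envelope opening, posture, fundal pressure and delivery time.

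**The case against.** The strongest reply is that nothing here is wrong. A t-test in a randomized trial is unbiased, it matches the sample-size calculation, and Step 1 shows the planned power is reached without covariates. That stands, and it limits the point to efficiency.

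A second reply is that adjustment belongs in the statistical analysis plan, which Data management and quality assurance says will be finalised before recruitment. This holds in part. That plan may well add an adjusted analysis, and the absence of a covariate list from the article is not the complaint. But the article names the test for this outcome, and the named test is unadjusted.

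A third reply is that the gain may be trivial. At R² = 2% it is: 91.9% to 92.5%.

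Three stronger readings are tempting, and the document does not support them:
- *That elapsed second-stage time is already on file.* The entry rule means staff must know it roughly, and second-stage duration appears in the objectives, but recording is nowhere stated.
- *That augmentation as captured is a baseline covariate.* Its timing is not given, so some of it may follow randomization.
- *That adjustment would rescue GAP versus upright alone.* On the plan's figures, power there moves only from about 27% to between 27% and 32%.

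Nor does chance imbalance make the t-test biased; its standard error already allows for it.

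**Conclusion.** The point holds as a low-cost improvement. The protocol commits the comparison of mean time to delivery to an unadjusted test while collecting baseline information that could sharpen it. For the 3-min target the gain is between 0.6 and 3.8 percentage points of power (R² from 2% to 15%), and the standard error falls by about 1% to 8%. If non-compliance dilutes the target to 2.7 min, unadjusted power is about 85%, and adjustment restores 90% only near R² = 15%. These figures rest on the plan's borrowed SDs, two-sided alpha 0.05/3, 382 analysed women per arm and an assumed R². The unadjusted result would remain valid.

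**What to change.** Before any outcome data are seen, prespecify as the primary analysis a linear model of minutes from randomization to delivery on:
- arm;
- induction or augmentation begun before randomization (yes/no);
- minutes of second stage elapsed at randomization, only if this is recorded;
- site, which can enter the same model because the envelopes are prepared by site.

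Report the three pairwise differences in mean minutes with robust standard errors. State that oxytocin started after randomization is not adjusted for. Keep the t-test as a supporting analysis, and say how the existing transformation rule relates to a model on raw minutes.

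The cost is a sentence or two in the analysis section and no extra women. The forms should be checked to confirm that augmentation can be dated relative to randomization. If it cannot, or if elapsed time is wanted, one timing item has to be added.

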## Discussion

### Expected outcomes of this study

The current widespread use of uncontrolled fundal pressure is an important public health and human rights issue, which this trial will seek to address. The study will establish whether upright posture and/or a controlled method of applying fundal pressure (GAP) can improve labour outcomes for women and/or their babies. If fundal pressure is found to have a measurable beneficial effect in this study, this gentle approach can be promoted as a replacement for the uncontrolled methods currently in use. If it is not found to be useful in this study, fundal pressure can be discouraged.

### Dissemination

The investigators are committed to the widespread dissemination of the findings of this study. We will seek to publish the results in a peer-reviewed journal, in addition to making the results available to the country Department of Health, to inform labour care policy and training. Study data will also be incorporated into our review of fundal pressure in the Cochrane Library, which is recognised as a leading source of evidence-based information. The review will appear in the WHO Reproductive Health Library, which is freely available on the internet in developing countries, and in several languages.

### Anticipated problems and solutions

The main potential problem that we anticipate may be a slow rate of recruitment. To minimize this possibility, dedicated research staff will be appointed at the recruiting sites. In addition, recruitment will be closely monitored and, if inadequate, consideration will be given to including additional sites or extending the duration of the study. The trial procedures are straightforward and have been shown in a pilot study to be feasible. As posture during labour is a potential confounding factor for studies of fundal pressure, we have eliminated the potential for this variable to confound results by designing a three-arm trial.

### Project management

This project will be managed by the UNDP/UNFPA/UNICEF/WHO/World Bank Special Programme of Research, Development and Research Training in Human Reproduction (HRP), Department of Reproductive Health and Research, World Health Organization, Geneva, Switzerland. In South Africa, the country principal investigators will establish the research teams that will implement the research activities. The study coordinating unit in Geneva will conduct site visits before and during the implementation of the study to contribute to study site selection, training workshops and assessment of adherence to study protocols. There will be continuous communication between country research teams and study coordinating unit at the WHO. Regular contact will be made to ensure that the timeline are followed and problems solved without delay.

A Data Safety Monitoring Committee (DSMC) will be established to safeguard the interests of the trial's participants, potential participants, investigators and sponsors, to assess the safety and efficacy of the trial's intervention according to adverse event data available while the trial is ongoing, and all other data available at a predefined schedule, to monitor the trial's overall conduct and quality, and protect its validity and credibility and to make recommendations concerning continuation or termination of study or any other modification necessary based on the observed effects of the intervention.

### Ethical considerations

The main ethical consideration relates to the timing of recruitment. The WHO RHR and the Effective Care Research Unit have extensive experience in recruitment of women for interventions around the time of childbirth. These trials have shown that it is feasible to recruit women in early labour, and that it is acceptable to women.

All women will receive information about the trial in their language of choice, conforming to ethical requirements for research involving human subjects. The language is non-technical and easily understood. Participants will be given time to reflect on the information. After signing the informed consent form, participants will be free to withdraw from the trial at any stage without loss of benefits. If a woman is illiterate, an impartial witness will be present during the entire informed consent reading and discussion. The impartial witness will also sign and date the ICF, along with the individual who performed the informed consent discussion. The telephone numbers of investigators will be made available participants in the event that they require further information or assistance.

There will be no payment for participation. Only compensation for time spent completing trial procedures as approved or requested by local ethics committees to be appropriate and non-coercive will be considered.

The study protocol (WHO Study A65866) was reviewed and approved by the WHO Research Project Review Panel (RP2) and the WHO Ethics Review Committee. Ethics The University of the Witwatersrand Committee for Research on Human Subjects (HREC) has approved this study protocol (Ethics clearance certificate no. M131054).

## Abbreviations

AE: Adverse event
ASCII: American standard code for information interchange
CONSORT: Consolidated standards of reporting trials
CRF: Case report forms
DSMC: Data safety and monitoring committee
ECRU: Effective care research unit
GAP: Gentle assisted pushing
GCP: Good clinical practice
ICF: Informed consent form
ICRHK: International centre for reproductive health Kenya
ID: Identification
PI: Principal investigator
SAE: Serious adverse event
SAS: Statistical analysis software
SIS: Statistics and informatics services
TSC: Trial steering committee
WHO: World health organization
